### 2.4 Eligibility criteria

#### 2.4.1 Inclusion criteria

Age ≥ 18 years.Histomolecular diagnosis of LrGG according to the 2021 WHO classification, regardless of prior oncological treatments.Eastern cooperative oncology group performance status (ECOG-PS) score ≤ 2.Neurosurgical resection (excluding biopsy) performed ≥12 months before inclusion.Cancer treatment (chemotherapy or radiation therapy) completed at least 6 months before inclusion.Cognitive complaints defined at least as “*Quite*” on items 20 and/or 25 of the EORTC QLQ-C30 questionnaire (i.e., “Cognitive Functioning” subscale score ≤ 66.67).Patient fluent in French.Patient covered by the French Social Security system.Regular use of digital tools and internet access.Signed informed consent.

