### 2.5 Sample size

To identify clinically meaningful improvements, responders will be defined as patients who show a FACT-Cog PCI score reduction of at least 6.5 points between baseline and M4. This threshold is based on previously validated minimal clinically important differences observed in patients with cancer, and estimated from the results of the TémoIN trial (NCT03257618) (Darlix et al., 2024) and the study by (Bray et al. 2017). A sample size of 168 evaluable patients is required to detect a 6.5-point mean difference in the FACT-Cog PCI score (control: 50, intervention: 56.5) with 80% power, two-sided α = 0.05, and an assumed standard deviation of 14 (Darlix et al., 2024; Bray et al., 2017). To take into account drop-outs, a conservative attrition rate of 10% was considered for this clinically stable LrGG population. This rate is consistent with attrition benchmarks in glioma trials, but it is likely to overestimate losses in cohorts of patients with clinically stable LrGG that are generally characterized by higher retention. Participation burden (many questionnaires at multiple time points) was also taken into account.

Therefore, 187 patients will be enrolled (187 × 0.90 = 168 patients evaluable at M4 for the primary endpoint). Based on prior observations from the TémoIN study (NCT03257618) showing that ~50% of screened patients were eligible, 374 patients will be screened over 24 months to reach the planned sample size (*n* = 187).

For the secondary endpoints, cumulative attrition is conservatively projected as follows: =10% by M6, =15% by M12, and =20% by M18. These estimates reflect modest progressive losses to follow-up, but also take into account the relative functional stability of patients with LrGG and the planned retention strategies (flexible schedule, family caregiver engagement, proactive follow-up). Sample size targets and the resulting evaluable number of patients were adjusted to align with these timepoint-specific attrition expectations, ensuring sufficient power for the primary and secondary analyses. Using these estimates, the expected number of evaluable participants at each scheduled assessment is reported in Figure 2.

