### 2.6 Randomization

Patients will be randomized in a 2:1 ratio (intervention: control) using a random block randomization method. This approach will maximize the number of patients who can benefit from the FREEDOME program. Stratification factors include:

Number of treatment lines (chemotherapy or radiotherapy, 0 vs. 1–2 vs. > 2);Baseline FACT-Cog PCI score (cognitive complaints) and HADS (distress) score (PCI score ≤ 47 and/or HADS score ≥13/42 vs. PCI score >47 and HADS score <13/42);Tumor histological grade (grade 2 vs. 3).

Investigators will register patients using the online electronic case report form (Ennov Clinical^®^).

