### 2.13 Data analysis

A statistical analysis plan will be drafted before database locking. For the for primary endpoint, all statistical analyses will be done using the intention-to-treat population and the evaluable population (i.e., patients with a FACT-Cog PCI score at baseline and M4).

Frequencies (N) and percentages (%) will be used to describe qualitative variables, and missing data reported. Percentages will be calculated after excluding missing data. Number of observations (N), median, minimum, maximum, mean, standard deviation, and interquartile range will be used to describe quantitative variables.

Baseline demographic and clinical characteristics, interventions and concomitant treatments will be described.

Questionnaire scores will be calculated according to established guidelines: FACT-Cog (Lange et al., 2016), QLQ-C30 and BN20 (EORTC manual), PRMQ (Guerdoux-Ninot et al., 2019), and neurocognitive and psychopathological tests (Gentile et al., 2003; Savard et al., 2005; Razavi et al., 1990; Beck et al., 1996; Bellaert et al., 2022; Nasreddine and Patel, 2016; Wechsler, 2011; Rieu et al., 2006; Bayard et al., 2023; Prevost et al., 2014; Spielberger, 1983; Guilmette et al., 2020). Scores will be reported and missing data rates recorded at all time points. Adherence rates will be estimated with their 95% confidence intervals.

The primary endpoint (FACT-Cog PCI score at M4) will be compared between arms with the Student's *t*-test or Wilcoxon/Mann-Whitney rank-sum test. An ANOVA or ANCOVA model will be used to adjust for potential confounders. A 5% significance threshold will be applied.

For the secondary endpoints:

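### The cognitive-complaint inclusion criterion equates an item rule with a subscale score of 66.67 or lower, but the two differ for one response pattern: one level below *Quite* on both items

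*Protocol article*

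**What the plan says.** The inclusion criteria (protocol article, section 2.4.1) require cognitive complaints, defined as an answer of at least *Quite* "on items 20 and/or 25 of the EORTC QLQ-C30 questionnaire (i.e., “Cognitive Functioning” subscale score ≤ 66.67". The part in parentheses restates the item criterion as a score. The connecting 'i.e.' tells the reader that either form can be used. No other section says which form governs.

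The article does not print the scoring formula. Section 2.13 refers scoring to published guidance, naming "QLQ-C30 and BN20 (EORTC manual") for this questionnaire.

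**The concern.** An eligibility criterion should give the same answer whichever of its stated forms is applied. A subscale score built from two items records only their sum, whereas the item rule depends on the higher of the two answers. Rules of these two kinds seldom coincide, so the claimed equivalence needs checking.

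What is at stake is who may be enrolled. This criterion selects for the complaint that the intervention targets and that the primary endpoint measures. The trial is multicentre (section 2.1), and eligibility may be confirmed by a neuro-oncologist or by an onco-neuro-psychologist (section 2.7). If one assessor reads the item answers and another reads the computed score, the same patient could be accepted at one centre and refused at another, with both assessors following the text.

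**Working it through.** **Inputs**

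- Item rule (section 2.4.1): at least *Quite* on item 20, item 25 or both.
- Score rule (section 2.4.1): Cognitive Functioning score of 66.67 or lower.
- Scoring (assumption, not printed in the article): each item takes levels 1 to 4, *Quite* is level 3, and with answers a and b

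  score = 100 × (1 − ((a + b)/2 − 1)/3).

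  Each one-level step on either item therefore costs 100/6 = 16.67 points.

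**Reproducing the cut-off.** The highest score that meets the item rule comes from *Quite* on one item and the lowest level on the other: (1,3) has mean 2, and 100 × (1 − 1/3) = 66.67. This matches the printed figure.

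**Enumeration of all answer pairs**

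| Answers (either order) | Score | Item rule | Score rule |
|---|---|---|---|
| 1,1 | 100 | no | no |
| 1,2 | 83.33 | no | no |
| 1,3 | 66.67 | yes | yes |
| **2,2** | **66.67** | **no** | **yes** |
| 1,4 | 50 | yes | yes |
| 2,3 | 50 | yes | yes |
| 2,4 | 33.33 | yes | yes |
| 3,3 | 33.33 | yes | yes |
| 3,4 | 16.67 | yes | yes |
| 4,4 | 0 | yes | yes |

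Counting ordered pairs, the item rule admits 12 of 16 and the score rule 13 of 16. The mismatch runs one way: meeting the item rule implies meeting the score rule, but not the reverse.

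**Can another cut-off repair it?** No. (2,2) and (1,3) have the same score, so any threshold treats them alike, while the item rule separates them. Using a score strictly below 66.67 removes (2,2) but also removes (1,3) and (3,1), which meet the item rule.

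**How much depends on the scoring assumption?** Suppose two equally weighted, evenly spaced items with K levels each, and let *Quite* lie q steps above the lowest level. For *Quite* plus the lowest answer to score 66.67, the loss must be one third of the scale: q/(2(K − 1)) = 1/3, so q = 2(K − 1)/3. With q = 1 this needs K = 2.5, which is impossible. With q = 2 it gives K = 4, the scale used above. On five levels with *Quite* third, (1,3) would score 100 × (1 − 1/4) = 75; the item rule would then admit (1,3) and (3,1) while the score rule refused them. The rules would still disagree, on a different pattern, and the printed cut-off would no longer correspond to the item rule.

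**Does it touch the sample size?** Section 2.5 uses a "6.5-point mean difference in the FACT-Cog PCI score (control: 50, intervention: 56.5"). Its other inputs are a power of 80%, a two-sided 5% level and an SD of 14. At the 2:1 allocation of section 2.6, controls = (1 + 1/2) × 14² × (1.960 + 0.842)² / 6.5² ≈ 54.6, rounded up to 55, or 165 in total against the 168 stated. The complaint rule does not enter this calculation.

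**The case against.** The strongest reply is that the criterion already has a governing rule. The complaint is defined by the item answers, and the score is only a gloss in parentheses. The gloss is true in one direction, since everyone who meets the item rule scores 66.67 or lower. The looser reading arises only if a site treats the parenthesis as a test in its own right, and nothing shown indicates that any site does. The full protocol and the eCRF checks are not shown and may settle the matter. The scoring formula is also assumed rather than quoted.

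Much of this stands. Divergent application across centres is possible, not demonstrated, and only one response pattern is affected. But 'i.e.' asserts equivalence, not a one-way implication, and an assessor who relies on the score is following the printed text. This is also not detail that an article has left out: both rules are printed, and they conflict. As for the formula, the cut-off itself fits four-level linear scoring, and the five-level alternative that was checked does not bring the two rules into agreement.

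**Conclusion.** The point holds in a narrow form. Under linear scoring of two four-level items, the item rule and the score rule disagree on exactly one response pattern, (2,2), which qualifies by score only. No cut-off on the two-item score reproduces the item rule, so one rule has to be named.

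A reader might infer more than the documents support:

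- *That anyone answering below* Quite *on both items qualifies by score.* This is not so: (1,1) and (1,2) score 100 and 83.33 and fail both rules.
- *That the score rule lets in the mildest complainers and so dilutes the treatment effect.* On the subscale, (2,2) scores the same as (1,3), which both rules admit. The primary endpoint is a different instrument, the FACT-Cog PCI, and nothing in the article links the answers to items 20 and 25 with PCI level or with room to improve.
- *That a number of affected patients can be given.* The frequency of (2,2) is not stated. Section 2.5 gives only an overall eligibility rate of about 50% among those screened, so the effect on enrolment cannot be quantified.
- *That the comparison is biased.* Eligibility is decided before randomisation, so any such patients may fall in either arm. The validity of the comparison and the sample-size arithmetic are unaffected.

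What remains is an ambiguity about who is eligible, and hence about the population to which the result applies.

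**What to change.** Reconcile the two statements in section 2.4.1:

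1. Establish which rule the centres have applied since recruitment opened in June 2024.
2. Name that single rule as operative. The documents do not settle which it should be.
3. Delete or correct the 'i.e.'. If the item rule governs, remove the score or describe it as a consequence of the rule, not an equivalent. If the score rule governs, reword the item description so that it covers the (2,2) pattern.
4. Check eligibility in the eCRF against the named rule.

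The cost is a one-line clarification and one eCRF check. If the item rule governs, slightly fewer screened patients may be eligible. Section 4 requires ethics committee approval for substantial amendments, so the sponsor would need to judge whether the change counts as one.

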#### 2.4.2 Non-inclusion criteria

Vision or hearing impairment preventing the use of computer tools (lateral homonymous hemianopia is not an exclusion criterion).Participation in another study with neurocognition as the primary outcome.Legal incapacity or conditions preventing consent obtention or study completion.Unstable psychiatric disorder (psychotropic drugs are not an exclusion criterion if doses are stable).Severe cognitive impairment (e.g., neurodegenerative disease, sequelae of traumatic brain injury), MoCA score ≤ 20/30 (Nasreddine and Patel, 2016), or impaired ability to use digital tools at home.Planned oncological treatment within 4 months of inclusion (isocitrate dehydrogenase- targeted therapies are allowed).

### 2.5 Sample size

To identify clinically meaningful improvements, responders will be defined as patients who show a FACT-Cog PCI score reduction of at least 6.5 points between baseline and M4. This threshold is based on previously validated minimal clinically important differences observed in patients with cancer, and estimated from the results of the TémoIN trial (NCT03257618) (Darlix et al., 2024) and the study by (Bray et al. 2017). A sample size of 168 evaluable patients is required to detect a 6.5-point mean difference in the FACT-Cog PCI score (control: 50, intervention: 56.5) with 80% power, two-sided α = 0.05, and an assumed standard deviation of 14 (Darlix et al., 2024; Bray et al., 2017). To take into account drop-outs, a conservative attrition rate of 10% was considered for this clinically stable LrGG population. This rate is consistent with attrition benchmarks in glioma trials, but it is likely to overestimate losses in cohorts of patients with clinically stable LrGG that are generally characterized by higher retention. Participation burden (many questionnaires at multiple time points) was also taken into account.

Therefore, 187 patients will be enrolled (187 × 0.90 = 168 patients evaluable at M4 for the primary endpoint). Based on prior observations from the TémoIN study (NCT03257618) showing that ~50% of screened patients were eligible, 374 patients will be screened over 24 months to reach the planned sample size (*n* = 187).

For the secondary endpoints, cumulative attrition is conservatively projected as follows: =10% by M6, =15% by M12, and =20% by M18. These estimates reflect modest progressive losses to follow-up, but also take into account the relative functional stability of patients with LrGG and the planned retention strategies (flexible schedule, family caregiver engagement, proactive follow-up). Sample size targets and the resulting evaluable number of patients were adjusted to align with these timepoint-specific attrition expectations, ensuring sufficient power for the primary and secondary analyses. Using these estimates, the expected number of evaluable participants at each scheduled assessment is reported in Figure 2.

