Patient adherence (i.e., completing at least 25 h of the recommended 40 h of the digital program and attending three telehealth consultations). The 25-h threshold is based on the study by (Bray et al. 2017), where the FACT-Cog PCI score change was higher in participants who trained >25 h than in those who trained <25 h (16.3 vs. 12.6 points). The three telehealth sessions (at the intervention start, mid-point, and end) will ensure sufficient therapeutic support, address barriers, and will allow reviewing progress and delivering personalized recommendations.Comparison of the FACT-Cog PCI scores (Lange et al., 2016) at baseline, M6, M12, and M18.Comparison of the scores the three other FACT-Cog subscales at baseline, M4, M6, M12, and M18.Comparison of the Prospective and Retrospective Memory Questionnaire (PRMQ) scores (Guerdoux-Ninot et al., 2019) at baseline, M4, M6, M12, and M18.Comparison of the EORTC QLQ-C30 scores (Aaronson et al., 1993) and its module Brain-20 (BN20) scores (Taphoorn et al., 2010) at baseline, M4, M6, M12, and M18.Comparison of the 20-item Multidimensional Fatigue Inventory (MFI-20) (Gentile et al., 2003) and the Insomnia Severity Index (ISI) (Savard et al., 2005) scores at baseline and M4, M6, M12, and M18.Proportion of patients returning to work or increasing their work hours at M4, M6, M12, and M18.Changes in self-rated psychological distress, depression, anxiety and irritability between baseline and M4, M6, M12, and M18 using the Hospital Anxiety and Depression Scale (HADS) (Razavi et al., 1990), Beck Depression Inventory-II (BDI-II) (Beck et al., 1996), State-Trait Anxiety Inventory-Y (STAI-Y) (Bellaert et al., 2022), and Brief Irritability Test (BITe) (Bellaert et al., 2022), respectively.Differences (between baseline and M4 and M12) in the clinician-rated scores of the following neurocognitive tests: Montreal Cognitive Assessment (MoCA) (Nasreddine and Patel, 2016), Working Memory Index [score derived from the Digit Span and Arithmetic subtests of the Wechsler Adult Intelligence Scale, Fourth Edition (WAIS-IV)], Processing Speed Index (from the Coding and Symbol Search subtests of the WAIS-IV) (Wechsler, 2011), Hopkins Verbal Learning Test (global scores) (Rieu et al., 2006), Standard Executive Neuropsychological Test Battery (Bayard et al., 2023) (including the modified Stroop Delis-Kaplan test, the Digit Span subtest of the WAIS-IV, the Verbal Fluency Test, the Trail Making Tests A and B), and Reading the Mind in the Eyes Test (Prevost et al., 2014).Correlations between the FACT-Cog sub-scores or PRMQ scores and key neurocognitive domains (global functioning, executive functions, language, working memory, processing speed, and social cognition) at baseline, M4, and M12.

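### The responder rule in section 2.5 has the wrong sign: it asks for a fall in FACT-Cog PCI, while the plan's own figures make a higher score the better one

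*Protocol article*

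**What the plan says.** Section 2.5 (Sample size) opens with a patient-level definition whose purpose is explicit: "To identify clinically meaningful improvements, responders will be defined as" those whose PCI falls, that is, "patients who show a FACT-Cog PCI score reduction of at least 6.5 points between baseline and M4".

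The same paragraph then states that 168 evaluable patients are "required to detect a 6.5-point mean difference in the FACT-Cog PCI score", with expected values "control: 50, intervention: 56.5" and "an assumed standard deviation of 14".

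Section 2.6 (Randomization) combines PCI with HADS, which it labels as distress, in one stratification factor: "PCI score ≤ 47 and/or HADS score ≥13/42 vs. PCI score >47 and HADS score <13/42".

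Section 2.3 (Endpoint measures) names the PCI score at M4 as the primary endpoint but does not say in words whether high or low is good. To justify the 25-hour adherence threshold, it reports from the cited trial of the web-based program that the "FACT-Cog PCI score change was higher in participants who trained >25 h than in those who trained <25 h" (16.3 vs. 12.6 points).

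**The concern.** The responder sentence and the planning assumption use the same score, the same 6.5 points and the same timepoint, but with opposite signs. If the intervention is hoped to bring patients to 56.5 rather than 50, a rise is the benefit, and a rule that requires a fall selects patients who deteriorate.

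The rule is stated prospectively and is the article's only patient-level definition of meaningful improvement on the primary instrument. A responder table programmed from it would count worsening patients as successes and, if the program works as planned, would favour control. The name of the subscale, Perceived Cognitive Impairment, makes the slip easy to miss, because it suggests that a high score is bad. Section 2.13 keeps the analysts of the primary outcome blinded to allocation. If they also produced such a table, the reversal might not be noticed until unblinding, and a correction at that stage would look post hoc.

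**Working it through.** **1. Reproduce the plan's sample size.** Inputs from sections 2.5 and 2.6: difference 6.5, SD 14, two-sided α 0.05, power 80%, allocation 2:1, attrition 10%.

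- Normal approximation, control arm: n = (1 + 1/2) × 14² × (1.96 + 0.8416)² / 6.5² = 1.5 × 196 × 7.849 / 42.25 ≈ 54.6, so 55. With 110 in the intervention arm the total is 165.
- Noncentral t: 55 + 110 gives 79.8% power and 56 + 112 = 168 gives 80.5%, so 168 is reproduced exactly.
- Attrition: 168 / 0.90 = 186.7, so 187. Conversely, 187 × 0.90 = 168.3.

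The test is two-sided, so the calculation depends only on the absolute difference. Power at 56 + 112 is the same for +6.5 and −6.5, and the responder rule does not enter.

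**2. Establish the direction of the score from the document.**

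| Place | Content | What it implies |
|---|---|---|
| 2.5, planned means | control 50, intervention 56.5 | benefit is a higher PCI |
| 2.6, strata | PCI ≤ 47 grouped with HADS ≥ 13; PCI > 47 with HADS < 13 | low PCI is the worse state |
| 2.3, adherence threshold | change of 16.3 vs. 12.6 points, no sign given | compatible with a rise as benefit, but does not establish it |
| 2.5, responder rule | fall of at least 6.5 is improvement | opposite to the first two rows |

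The first two rows are enough. The article describes no reversed scoring under which a fall would be an improvement.

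**3. Apply the rule to single patients.** A patient going from 50 to 43.5 changes by −6.5 and is a responder as written. A patient going from 50 to 56.5 changes by +6.5 and is not.

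**4. Illustrate the effect on responder rates.** These assumptions are not in the document: normal change scores, mean change 0 in control and +6.5 in intervention, and baseline-to-M4 correlation r. The SD of change is 14 × √(2(1 − r)), which equals 14 at r = 0.5.

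At r = 0.5:
- Written rule, control: Φ(−6.5/14) = 0.321.
- Written rule, intervention: Φ((−6.5 − 6.5)/14) = Φ(−13/14) = 0.177.
- Sign corrected, control: 1 − Φ(6.5/14) = 0.321.
- Sign corrected, intervention: 1 − Φ(0) = 0.500.

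| r | SD of change | Written rule: control vs intervention | Sign corrected: control vs intervention |
|---|---|---|---|
| 0.3 | 16.57 | 34.7% vs 21.6% | 34.7% vs 50% |
| 0.5 | 14.00 | 32.1% vs 17.7% | 32.1% vs 50% |
| 0.7 | 10.84 | 27.4% vs 11.5% | 27.4% vs 50% |

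Across this range the written rule makes a program that performs as planned look inferior.

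**The case against.** The strongest reply is that the sentence drives nothing. The responder definition appears only in section 2.5. It is not among the primary, secondary or exploratory endpoints in section 2.3, and section 2.13 describes no responder analysis. The primary comparison is of PCI scores at M4, by t-test or rank-sum test with possible ANOVA or ANCOVA adjustment. This stands and sets the limit of the point. A reader might infer that the error reverses the trial's conclusion or undermines its power. The documents do not support that, because neither the primary test nor the 168/187 calculation uses the rule.

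A second reply is that the intent can be recovered. The sentence announces improvement, the planned means follow shortly after, and section 2.13 says that questionnaires will be scored by established guidelines and that an SAP will be drafted before database lock. The authors may have meant a reduction in perceived impairment. This lowers the risk of a wrongly signed analysis, but the sentence says that the score falls, and section 2.3 gives no score direction to check it against.

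A third reply concerns the evidence. A reader might also count the adherence figures in section 2.3 as independent proof of direction. They are unsigned and could be sizes of change either way, so the argument does not rest on them.

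**Conclusion.** The point holds as an internal contradiction in a prospectively stated definition. By the planned means in section 2.5 and the strata in section 2.6, a higher PCI is better, so the responder rule as written identifies deterioration. The damage is confined to any responder analysis or statement of clinical relevance that relies on it. The primary endpoint, its test and the sample size are sound in this respect.

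The contrast of about 32% vs 18% as written with 32% vs 50% after correction shows what such an analysis would report if the planned effect were real. It rests on the assumed mean changes, normality and an SD of change of 14. It is not an estimate of an effect on any analysis the article lists.

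**What to change.** In section 2.5, define responders by an increase, not a reduction, of at least 6.5 points in FACT-Cog PCI between baseline and M4. In section 2.3, state once that a higher PCI score means less perceived impairment. Carry the same sign into the SAP and its programs before database lock. If a responder analysis is intended, it should use the corrected definition.

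The cost is one changed word and one added sentence. Sample size, data collection and the primary analysis stay as they are.
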